#### **Background**

Neck pain is a common and challenging health problem in the world population, with average lifetime prevalence of 48.5% [1]. It is experienced by people of all ages, with the 12-month prevalence of any neck pain among adults ranged from 12.1% to 71.5% and among children ranged from 34.5% to 71.5% [2].

In Hong Kong, neck pain was highly prevalent with increasing impact [3-4]. The 12-month prevalence of neck pain was 64.6% and around 38.0% suffered from moderate to severe pain [4]. Neck pain caused disturbances to social and work functions. There were about 17.7% of these neck pain patients had to limit their social activities and 19.0% had to limit their work [4]. Moreover, approximately 25.0% of neck pain patients have consulted medical or health professionals and it demonstrated a general trend that more neck pain patients used complementary therapies, including acupuncture [3-4].

There are different types of definitions and classification for neck pain in literature based on anatomical location, etiology, severity, and duration of symptoms [5]. According to the Bone and Joint Decade 2000-2010 Task Force on Neck Pain and Its Associated Disorders, neck pain was specific to pain located in the anatomic region of the neck, with or without radiation to the head, trunk and upper limbs [6]. The

anatomic region of the neck from the back referred to the region from the superior nuchal line to the spine of the scapula and the anatomic region of the neck from the side referred to the region from the superior nuchal line down to the superior border of the clavicle and the suprasternal notch.

There are various invasive and noninvasive treatment options available for patients with neck pain, including medications, injection, manual therapies, physical modalities, complementary and alternative medicine therapies, education or advice, and surgery [7-8]. However, due to the paucity of evidence from primary studies, the efficacy of currently available treatments for neck pain remains unclear [9-10].

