### ***Inclusion criteria***

Patients will be included in the study if they satisfied the following criteria:

- between 18 and 65 years of age with the ability to speak and understand Cantonese;

- neck complaints on:
  - pain, stiffness or tenderness, with or without musculoskeletal signs including decreased range of motion and point tenderness [22];
  - pain felt in the neck with radiation to the occiput or towards the shoulders, or both with limitation of neck motion [22];
  - neck pain with degenerative joint disease or cervical spondylosis, or both [22];
- 3 points or more on a 10-cm visual analogue scale for neck pain at the time of screening;
- no previous treatment with abdominal acupuncture for any reason;
- agreed to be randomized; and
- agreed to sign the informed consent form.

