### ***Outcome measurements***

#### ***Baseline information***

Sociodemographic information of all participants, including age, gender, education background and neck pain history including pain sites (unilateral neck, bilateral neck, central neck), pain duration, pain occurrence, previous neck injury, and previous neck treatments, will be recorded at baseline interview. An outcome assessor who is masked to treatment allocation will conduct assessments.

The study's primary endpoint will be immediately after the intervention ends. Table 1 below summarizes the categories of information and measurements that are included in the baseline and follow-up interviews.

Table 1. Content of baseline and follow-up assessments

| Measures                                   | Baseline | Finished | 4-week | 12-week |
|--------------------------------------------|----------|----------|--------|---------|
| Inclusion and exclusion variables          | X        |          |        |         |
| Sociodemographic characteristics           | X        |          |        |         |
| Neck pain history                          | X        |          |        |         |
| Neck Pain Questionnaire - Real             | X        | X        | X      | X       |
| - Sham                                     | X        | X        | X      |         |
| VAS for pain intensity † - Real | X        | X        | X      | X       |
| - Sham                                     | X        | X        | X      |         |
| SF-36v2 Health Survey - Real               | X        | X        | X      | X       |
| - Sham                                     | X        | X        | X      |         |
| Credibility test                           | X        | X        |        |         |
| Satisfaction with treatment                |          | X        |        |         |
| Blinding assessment †           |          | X        |        |         |
| Use of medications *            | X        | X        | X      | X       |
| Adverse experiences *           |          | X        | X      | X       |
| Dropouts and withdrawals *      | X        | X        | X      | X       |

\* At every single visit; † After the first treatment

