#### *Statistical issues*

##### *Sample size determination*

The sample size will be determined with a general acceptance of probability of 0.05 in committing a type I error and a power of 80%. For two arms (control — sham abdominal acupuncture and experimental — real abdominal acupuncture), repeated measures of analysis of variance (ANOVA) model will be used. An effect size of 0.2, which considered as small by Cohen [42], will be adopted. By using the power analysis program G\*Power 3 [43] with consideration of equal allocation between the two groups and a dropout rate of 15%, it is estimated that each group will require 77 subjects, with a total sample size of 154 subjects for this study.

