### *Statistical methods and analysis*

Analyses of data in this study will be performed by using statistical analysis software (SPSS 20.0). Two-sided significance will be defined as  $P < 0.05$ .

All the demographic, clinical, baseline and adverse events data will be analyzed descriptively, using means and standard deviations and 95% confidence intervals (CIs) for the continuous variables and percentages for the categorized ones. These data will be performed separately for each study group. Baseline characteristics of all study groups will be compared to examine homogeneity. Independent two-sample t-test will be used to determine possible baseline differences for quantitative data. The Chi-square test will be used to determine possible differences for qualitative data.

An intention-to-treat approach will be used for all analyses in this study for all the randomized patients to assess the efficacy of abdominal acupuncture treatment. Missing data will be replaced with the last value obtained from the patients, and such value will be carried forward if no additional value obtained. This approach is based on the assumption that patients who have missing values do not have improvement since the last follow-up assessment and may expect no further benefit from the therapy.

Repeated measures ANOVA will be used as single overall tests for the effects of treatment and for the comparison between real and sham abdominal acupuncture groups at baseline, immediately after the intervention ends, and at 4-week follow-up interviews. The ANOVA will be performed for each outcome variable separately. Between groups effects of measurement for each outcome variable at different assessments will be analyzed by ANOVA while the difference of outcomes between

real and sham abdominal acupuncture groups will be assessed by the independent sample t-test.

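### The arms are compared with no covariate, although baseline NPQ and pain duration are both recorded, and the baseline significance tests cannot make up for it; the loss is precision, not validity

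*Protocol*

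**What the plan says.** **Eligibility.** The Background notes that neck pain is classified in several ways, "based on anatomical location, etiology, severity, and duration of symptoms". The inclusion list sets a severity threshold, "3 points or more on a 10-cm visual analogue scale for neck pain at the time of screening". Neither the inclusion nor the exclusion list sets a minimum or maximum duration of pain.

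**Data collected.** Under Baseline information, "pain duration, pain occurrence, previous neck injury, and previous neck treatments, will be recorded at baseline interview". Table 1 also schedules the NPQ, VAS and SF-36v2 at baseline in both arms.

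**Randomization.** Allocation is 1:1 in blocks of varying size. No stratification factor is named.

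**Analysis.** Under Statistical methods and analysis, "Baseline characteristics of all study groups will be compared to examine homogeneity", by t-test for quantitative and chi-square test for qualitative data. Nothing is said to follow from the result. Efficacy is then assessed by repeated measures ANOVA over baseline, end of intervention and 4 weeks, as the single overall test, and outcome differences between "real and sham abdominal acupuncture groups will be assessed by the independent sample t-test". No covariate is named in either. The text does not say whether the t-test uses raw values or changes from baseline. The primary time point, given under Baseline information, is the end of the intervention.

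**The concern.** The baseline tests look like a safeguard but do not act as one. After sound randomization any baseline difference is due to chance, so the test asks a question whose answer is already known, and a significant result corrects nothing. With 77 per arm it flags only differences above about 0.32 SD.

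The values that could sharpen the comparison are already collected. A pre-randomization variable that predicts the outcome, if left out of the model, stays in the residual variance, and any chance imbalance in it stays in the estimate. Baseline NPQ is the obvious first candidate. Pain duration is a reasonable second, because recent and long-standing pain may both enter and might change by different amounts over two weeks of treatment. At stake are the width of the confidence interval for the NPQ difference and some power.

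**Working it through.** **Inputs from the Protocol.** Two-sided alpha 0.05; power 80%; repeated measures ANOVA with two arms and no covariate; 15% dropout; 77 per arm, 154 in total (Sample size determination; Statistical methods and analysis). There are m = 3 measurements. On the effect, "An effect size of 0.2, which considered as small by Cohen [42], will be adopted"; the metric is not named.

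**Assumptions, not in the Protocol.** Correlation among repeated measures ρ = 0.5. Correlation r of pain duration with the outcome from 0.1 to 0.5.

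**1. Reproducing the stated sample size.** Read 0.2 as Cohen's f, which for two groups is d = 2f = 0.4. For the between-group test, λ = f²·N·m / [1 + (m − 1)ρ] with 1 and N − 2 degrees of freedom. At N = 134, λ = 0.04 × 134 × 3 / 2 = 8.04 and power is 0.804. Then 67 × 1.15 = 77.05 per arm, which is the stated 77. (Dividing by 0.85 would give 134 / 0.85 = 157.6, so 158; the difference does not affect this point.) The stated 154 therefore rests on an unadjusted model.

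**2. What adjusting for duration adds.** A covariate with correlation r multiplies the residual variance by 1 − r², so λ is divided by 1 − r² and the share of the sample saved is about r². The t-test column uses the normal approximation Φ(d / [√(1 − r²)·√(2/77)] − 1.96) with d = 0.4 on end-of-intervention values. For r = 0: 0.4 / 0.161 − 1.96 = 0.52, power 0.699.

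| r | share saved (r²) | N before dropout for 80% | power at 134 analysed | t-test power, 77 per arm |
|---|---|---|---|---|
| 0 | – | 134 | 0.804 | 0.699 |
| 0.1 | 1% | 132 | 0.808 | 0.703 |
| 0.2 | 4% | 128 | 0.819 | 0.717 |
| 0.3 | 9% | 122 | 0.839 | 0.740 |
| 0.5 | 25% | 102 | 0.901 | 0.818 |

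The confidence interval narrows by 1 − √(1 − r²): 0.5% at r = 0.1, 2.0% at 0.2, 4.6% at 0.3 and 13.4% at 0.5.

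**3. What the baseline test can see.** The smallest difference reaching P < 0.05 with 77 per arm is 1.976 × √(2/77) = 0.32 SD.

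**4. Chance imbalance in duration.** Its 95% limit is 1.96 × √(2/77) = 0.316 SD. Multiplied by r, this moves the outcome difference by 0.032, 0.063 or 0.095 SD at r = 0.1, 0.2 or 0.3. The 95% half-width of the unadjusted t-test comparison is also 0.316 SD and already contains this source of error.

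**5. Baseline NPQ.** The Protocol gives no correlation between baseline and end-of-intervention NPQ. If it were the 0.5 assumed in step 1, the same formula gives 1 − 0.5² = 0.75 of the variance of raw end-of-intervention values. The variance of change scores, 2(1 − 0.5) = 1, gives no gain over raw values. On that assumption ANCOVA on baseline NPQ improves on either form of the t-test. Whatever duration shares with baseline NPQ is then already removed, so the duration figures in step 2 may be too large as an additional gain.

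**The case against.** **Nothing in the Protocol shows that duration predicts NPQ.** This stands. The Background only lists duration among the ways neck pain is classified, and pain site, occurrence, previous injury and previous treatments are recorded as well. The figures for duration are therefore conditional on r, and they are small up to r = 0.3.

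**The unadjusted comparison is valid.** This also stands. A reader might infer that unlimited duration, together with unstratified randomization, biases the result or inflates type I error. It does not: allocation is random and the standard error already allows for chance imbalance in every factor. A reader might also set the 0.095 SD shift at r = 0.3 against d = 0.4 and conclude that about a quarter of the effect could be spurious (0.095 / 0.4 = 0.24). That shift is the 95% extreme of ordinary sampling error, well inside the half-width of 0.316 SD.

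**The overall test already uses the baseline visit.** This stands in part. In the group-by-time term of the repeated measures ANOVA, a stable effect of duration on NPQ level cancels; only an effect on change remains. The argument applies to that remaining part, to the between-group main effect (the term that reproduces 154), and to the t-test.

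**Covariates are commonly left to the SAP.** A SAP, not shown here, may name them. But the Protocol is not merely silent: it prescribes baseline significance tests and an efficacy t-test, which has no covariate. That is a stated method that can be improved, not a missing detail.

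**Conclusion.** The point holds as one of precision. The Protocol tests baseline characteristics to no effect and compares the arms without using as covariates the baseline values it collects. For pain duration alone, the gain from adjustment is about 1% to 9% of the sample at an assumed r of 0.1 to 0.3, or 0.4 to 3.5 points of power at 134 analysed. It is about 25%, or roughly 10 points (0.901 − 0.804), only if r is 0.5. These figures rest on assumed correlations and on the between-group test with ρ = 0.5; the additional gain may be smaller once baseline NPQ is included. The Protocol does not support a finding of bias, of invalid inference, or of eligibility that is too wide. The case for changing the plan is that the improvement costs almost nothing.

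**What to change.** 1. Report baseline characteristics by arm descriptively and drop the significance tests.
2. Estimate the real–sham NPQ difference at the end of the intervention by ANCOVA, or by a mixed model over the post-baseline visits, with baseline NPQ and pain duration as pre-specified covariates whatever the observed balance. Duration without baseline NPQ would leave out the obvious first covariate.
3. Fix the form of duration (log-transformed or set categories) before unblinding.
4. Do the same for VAS and SF-36v2, each with its own baseline value and pain duration.

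**Cost:** a sentence or two in the analysis section, two or three degrees of freedom out of about 152 (154 − 2), and the need to choose the form of duration in advance. No new data are needed, and eligibility and sample size do not change.

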## **Conclusion**

This is the first rigorously designed evidence-based clinical trial to evaluate whether abdominal acupuncture is more efficacious in relieving pain than non-penetrating sham abdominal acupuncture in patients with neck pain in Hong Kong. The results obtained in the proposed study would provide valuable information about the efficacy of abdominal acupuncture for neck pain and set a solid foundation for future full-scale clinical study on the same topic. The development of the abdominal acupuncture protocol through evidence-based approach would be very important in providing an efficacious alternative treatment method for further clinical management of neck pain.

